# Effects of whole-body vibration on sensorimotor deficits and brain plasticity among people with chronic ankle instability: a study protocol for a single-blind randomized controlled trial

**DOI:** 10.1186/s13102-023-00698-0

**Published:** 2023-07-18

**Keywords:** Whole-body vibration, Chronic ankle instability, Sensorimotor deficits, Brain plasticity, Study protocol, Randomized controlled trial

## Abstract

**Background:**

Chronic ankle instability (CAI) is a form of musculoskeletal disease that can occur after a lateral ankle sprain, and it is characterized by pain, recurrent ankle sprains, a feeling of “giving way” at the ankle joint, and sensorimotor deficits. There has been increasing evidence to suggest that plastic changes in the brain after the initial injury play an important role in CAI. As one modality to treat CAI, whole-body vibration (WBV) has been found to be beneficial for treating the sensorimotor deficits accompanying CAI, but whether these benefits are associated with brain plasticity remains unknown. Therefore, the current study aims to investigate the effect of WBV on sensorimotor deficits and determine its correlation with plastic changes in the brain.

**Methods:**

The present study is a single-blind randomized controlled trial. A total of 80 participants with CAI recruited from the university and local communities will be divided into 4 groups: whole-body vibration and balance training (WBVBT), balance training (BT), whole-body vibration (WBV), and control group. Participants will be given the WBV intervention (25-38 Hz, 1.3-2 mm, 3-time per week, 6-week) supervised by a professional therapist. Primary outcome measures are sensorimotor function including strength, balance, proprioception and functional performance. Brain plasticity will be evaluated by corticomotor excitability, inhibition, and representation of muscles, as measured by transcranial magnetic stimulation. Activation of brain areas will be assessed through functional near-infrared spectroscopy. Secondary outcome measures are self-reported functional outcomes involving the Cumberland Ankle Instability Tool and the Foot and Ankle Ability Measure. All tests will be conducted before and after the WBV intervention, and at 2-week follow-up. Per‑protocol and intention-to-treat analysis will be applied if any participants withdraw.

**Discussion:**

This is the first trial to investigate the role of brain plasticity in sensorimotor changes brought by WBV for individuals with CAI. As plastic changes in the brain have been an increasingly important aspect in CAI, the results of the current study can provide insight into the treatment of CAI from the perspective of brain plasticity.

**Trial registration:**

Chinese Clinical Trial Registry (ChiCTR2300068972); registered on 02 March 2023.

## Background

About 20–50% of people with a history of lateral ankle sprain may develop chronic ankle instability (CAI) [1, 2], which is characterized by pain, the feeling of "giving way" at the ankle joint, and recurrent ankle sprains [3]. In addition, CAI is accompanied by sensorimotor deficits [4], shown by reduced balance, strength, and muscle activity. The long-term sequelae of CAI are problematic, as it can lead to financial burdens [5], limited physical activity [6], and reduced health-related quality of life [7] for patients.

Despite the growing body of research evidence, the underlying mechanism of CAI is still unclear [3, 8, 9]. It was previously suggested that the sensory dysfunction that occurred after the initial lateral ankle sprain would affect sensorimotor function of patients with CAI [4]. However, the understanding of CAI has gradually evolved from a structural-pathology paradigm focusing on peripheral structural changes to a neurophysiological paradigm concentrating on the neuronal processing of noxious stimuli [10, 11]. According to theories proposed by Needle [9] and Heterl [3], it was speculated that peripheral sensory deficits such as inflammation, pain, instability, and laxity would lead to subsequent sensorimotor deficits through causing functional and structural changes in the brain. For instance, individuals with CAI were found to possess reduced corticomotor excitability in a transcranial magnetic stimulation test [12], different cortical activation evaluated by functional near-infrared spectroscopy [13], and an altered brain network revealed in resting-state functional magnetic resonance imaging [14]. Additionally, structural evidence has also been observed including microstructural damage in white matter [15], reduced grey matter volume [16] and impairment in the corticospinal tract [17]. The above alterations are important because they are closely related to the changes of sensorimotor deficits for patients with CAI [18–20]. Fortunately, these plastic changes can be restored through specific interventions. A recent study found that stroboscopic balance training could not only improve postural control, but also modulate cortical activities of CAI athletes [21]. Likewise, another study reported that transcutaneous electrical nerve stimulation was effective in modifying corticospinal excitability in individuals with CAI [22]. Accordingly, plastic changes in the brain should be considered when treating CAI symptoms.

Neuromuscular training, which usually refers to either proprioceptive drill, strength training, or a combination of both [23, 24], is an effective intervention modality in treating the sensorimotor deficits of individuals with CAI [25, 26]. However, it has not been fully determined as to which neurophysiological mechanism contributes the most to the benefits of neuromuscular training. Based on the existing hypothesis, the mechanism underlying the effect of neuromuscular training on sensorimotor deficits may be related to both spinal (e.g., altered H-reflex) and supraspinal adaptation (e.g., feed-forward reflexive mechanism) [4, 27, 28], yet relevant evidence is lacking for these hypotheses. As one form of neuromuscular training, whole-body vibration (WBV) has been widely studied in different areas such as sports [29], rehabilitation [30], and public health [31]. The possible mechanism of WBV benefits is that it could facilitate reflexive activation at both the spinal and supraspinal level in the central nervous system [32, 33]. To be specific, WBV has been shown to be capable of modulating spinal excitability in a human trial [34], and modulating synaptic plasticity [35, 36] and neurogenesis [37] in the brain of animals. Regarding the effectiveness of WBV for CAI, it has been found that additional benefits could be achieved in sensorimotor deficits (e.g., postural control, strength, and muscle activity) when WBV was added as a supplementary tool [38–40]. Nevertheless, it was still unknown whether the improvements in sensorimotor functions were associated with plastic changes in the brain for people with CAI. Investigation of the relationship between effectiveness of WBV and brain plasticity may provide understanding regarding the pathways through which WBV works on CAI [16].

Therefore, a single-blind randomized controlled trial will be designed to answer the following questions: (a) if WBV can generate sensorimotor benefits for patients with CAI? (b) is there a correlation between changes of sensorimotor functions and alterations of brain plasticity for participants with CAI? In this study, We hypothesize that there will be plastic changes in the brain after the WBV intervention, and these alterations will be correlated with changes in sensorimotor functions.

## Methods

### Study design and ethical approval

The present study is a single-blind randomized controlled trial designed following the.

Consolidated Standards of Reporting Trials (CONSORT, version 2010) [41], Standard Protocol Items Recommendations for Interventional Trials (SPIRIT, version 2013 [42, 43] and PRO Extension [44, 45]) (See supplementary file 1). The flowchart, schedule of enrollment, intervention and assessments are presented in Fig. 1 and Table 2 respectively. The research protocol has been approved by the Medical Ethics Committee of the Department of Psychology and Behavioral Science of Zhejiang University (NO. 2,022,095). In addition, the current study was registered at the Chinese Clinical Trial Registry (ChiCTR2300068972) on 02 March 2023.

**Fig. 1 Fig1:**
[figure not shown]
Flowchart showing participant recruitment, interventions, and assessments. Abbreviations: BT = Balance Training; IAC = International Ankle Consortium; WBV = Whole-Body Vibration; WBVBT = Whole-Body Vibration and Balance Training

### Participants

Participants will be recruited from universities and nearby communities. The selection criteria used in the recruitment procedure will be in accordance with the position statement of the International Ankle Consortium [46]. The inclusion criteria for the CAI group will be: (1) a history of at least one significant ankle sprain with the first sprain occurring at least 12 months before the study; (2) the sprain is associated with inflammatory symptoms (e.g., pain, swelling, etc.) and interrupts desired physical activities for at least 1 day; (3) participants report that there are at least two episodes of the ankle joint “giving way” and/or recurrent ankle sprains in the 6-month period before the study; (4) feeling of instability confirmed by the Cumberland Ankle Instability Tool (CAIT < 24), and the score < 90% in the section of activities of daily living and < 80% in the section of sports activities of the Foot and Ankle Ability Measure (FAAM). The exclusion criteria for the CAI group will be: (1) pregnancy; (2) vestibular or cognitive deficits; (3) neurological (e.g., concussion) or musculoskeletal (e.g., anterior cruciate ligament reconstruction) problems that probably affecting ankle movements or balance; (4) contraindications to participate in assessments such as transcranial magnetic stimulation (e.g., microprocessor implant, epilepsy).

### Randomization, allocation, and blinding

Concealed random allocation will be conducted by an independent researcher after the baseline testing using a sealed envelope filled with random numbers (1–99) generated by the software of Microsoft Excel.

Eligible participants will be allocated into 4 groups (Fig. 1):balance training (BT): undertaking balance training on the flat floor.whole-body vibration (WBV): standing on the vibration platform using one-legged stance and conduct the same tasks as BT group.whole-body vibration and balance training (WBVBT): performing balance training on the vibration platform.control group: no intervention.

Participants in all groups will be allowed to maintain their normal physical activity but avoid any therapeutic exercises of the ankle joint. As WBV stimulation can be easily felt, it is difficult to blind patients. Accordingly, blinding will only be performed on assessors.

### Intervention

The WBV intervention programs of this trial are structured according to previously published guidelines [47, 48] and will be conducted with the supervision of a professional therapist in the fitness center of Zhejiang University. In this study, the vibration stimulus will be generated in synchronous form by one platform with a handrail (Myo 2, Power Plate Corp., USA) and another one without a handrail (A6, TiFit Corp., China). Before the experiment, the participants will be instructed to perform a warm-up program consisting of 5-min of stretching and 5-min of bicycling. Verbal and visual instructions will be given to the participants before performing any sort of exercise. The limb with the lower CAIT score will be chosen if the individuals have bilateral CAI. The angle of the knee in the WBV group will be set at 20-30º to reduce the transmission of vibrations to the head as much as possible. The frequency (number of cycles per second) is adjustable and will be calibrated each time prior to the experiment using an accelerometer (66B, VICTOR Corp., China) placed at the central point of the platform surface. Table 1 indicates the intervention scheme used in the present study.

**Table 1 Tab1:** Six-week whole-body vibration intervention program for people with chronic ankle instability

Week	Exercise	Duration-set- rest period	Magnitude; Hertz
1	One-legged stance on the foam surface	60 s-5–60 s	1.3 mm; 25 Hz
2	One-legged stance on the BOSU	60 s-5–60 s	1.3 mm; 25 Hz
3	One-legged stance on the foam surface and holding a medicine ball head of the cheast (1 kg)	60 s-5–60 s	2 mm; 30 Hz
4	One-legged stance on the foam surface and throwing a medicine ball upwards (1 kg)	60 s-5–60 s	2 mm; 30 Hz
5	One-legged stance on the BOSU and holding a medicine ball head of the cheast (1 kg)	60 s-5–60 s	2 mm; 38 Hz
6	One-legged stance on the BOSU and throwing a medicine ball upwards (1 kg)	60 s-5–60 s	2 mm; 38 Hz

According to principles of neural plasticity, components including intensity, task-specificity, focus of attention, repetition, and duration will be modified to achieve the desired neuroplastic alterations [49, 50]. As a previous study found that a vibration frequency at 27 Hz rather than 10 Hz generated greater activation in the cerebral cortex [51], the vibration frequency spectrum will range from 25 to 38 Hz, with the magnitude (peak-to-peak displacement) of 1.3-2 mm to achieve the intensity of vibration stimulation. Balance training, in which participants stand on the foam or BOSU placed on the vibration platform, will be added to WBV intervention as a way of obtaining an increased degree of intensity. To meet the principle of task-specificity, participants in all experimental groups will be requested to stand with involved leg. External focus will be given by asking subjects to hold a medicine ball ahead of the chest as steady as possible and catch a medicine ball thrown upwards (5–10 cm of height) by the participants themselves. As for the repetition, the training program conducted 3-day a week will consist of 5 series of 60-s exercises with 60-s rest period between on each day [52, 53]. Previous study has found that acute WBV does not seem able to yield significant changes for individuals with CAI [54, 55], so a long-term training program lasting for 6-week will accordingly be scheduled, based on reference to previous studies [21, 39].

### Outcome measures

Sociodemographic information including name, sex, age, dominant leg, physical activity and level of kinesiophobia will be collected through online questionnaires. Self-reported measures consist of the CAIT and FAAM. Objective measures in the current study include sensorimotor function and brain plasticity. The primary outcome measures will be balance with SEBT end-point to determine sensorimotor deficit, and activation of brain area with oxyhemoglobin in determining brain plasticity. All measures of outcome will be performed by a qualified blinded assessor, who is independent of the current study, at the fitness laboratory of Zhejiang University. An adequate rest period, assessed with a rating of perceived exertion (Borg scale, 6–20), will be given between each of the two objective measures to avoid potential fatigue. Since TMS is potentially associated with alterations of functional performance, the test orders (Table 2) will be arranged to mitigate any mutual influence between each two tests. To avoid the influence of myopia on balance control, participants will be asked to wear any corrective eyewear throughout the test process. The extremity with the lower CAIT score will be tested if bilateral ankle instability exists. Outcome measures will be assessed before and after the WBV intervention. According to a previous study, there were delayed improvements in balance and self-reported functions for patients with CAIafter accepting balance training programs [56]. Hence, the follow-up assessments will be performed 2-week after the intervention program.

**Table 2 Tab2:** SPIRIT timetable including schedule of enrolment, interventions and assessments

	Study period					
	Enrolment	Baseline assessment	Allocation	Post-allocation	Post-intervention assessment	Follow-up
Time points	-4 to -1 weeks		0	1–6 Weeks	6–7 weeks	8–9 Weeks
Enrollment						
Eligibility screen	X					
Informed consent	X					
Random allocation			X			
Intervention						
WBV						
Assessment						
Primary outcome measures						
Brain activity						
Corticomotor Plasticity (TMS)		X			X	X
Activation of brain area (fNIRS)		X			X	X
Sensorimotor deficits						
Balance (SEBT&TIBT)		X			X	X
Strength (HHD)		X			X	X
Proprioception (AMEDA)		X			X	X
Functional performance (SHT)		X			X	X
Secondary outcome measures						
Ankle instability (CAIT)		X			X	X
Ankle function (FAAM)		X			X	X

Abbreviations: *AMEDA* Active Movement Extent Discrimination Apparatus, *CAI* Chronic Ankle Instability, *CAIT* Cumberland Ankle Instability Tool, *FAAM* Foot and Ankle Ability Measure, *HHD* Hand-Held Dynamometer, *fNIRS* Functional Near-Infrared Spectroscopy, *SEBT* Star Excursion Balance Test, *SHT* Side-Hop Test, *SPIRIT* Standard Protocol Items Recommendations for Interventional Trials, *TIBT* Time-In-Balance Test, *TMS* Transcranial Magnetic Stimulation, *WBV* Whole-Body Vibration

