### Sensorimotor deficits

Static balance will be estimated through the Time-In-Balance Test (TIBT). In the TIBT, participants will stand on a firm surface in a single-legged stance. Participants will be instructed to put their hands on their spina iliaca. The time taken to keep balance with eyes closed will be recorded and referenced with a cutoff score of 25.89 s [57]. The maximum duration of the test is 60-s [58]. The test will be carried out with 1 practice trial and 2 measured trials with a 60-s interval between each test. The longest time between the two tests will be recorded as the final score. The outcome will be discarded and replaced by a new test if: (1) participants move the tested foot; (2) the contralateral foot touches the floor.

Dynamic balance will be assessed using the Star Excursion Balance Test (SEBT), which is an effective means for determining reach deficits of CAI individuals [59]. There will be 8-direction including anterior, anteromedial, medial, posteromedial, posterior, posterolateral, lateral and anterolateral in the SEBT test. During the test, participants will be asked to stand at the center point using the involved limb and put their hands on their spina iliaca. Then, participants will be asked to use non-stance limb to reach in each direction as long as possible. In each direction, the farthest point of the great toe will be marked and recorded. The score will be discarded under the following conditions: (1) participants shift or lift the involved limb; (2) balance can not be maintained during the test. Before the official test, participants will have 2 practice trials to familiarize them with the test procedure and setting. To calculate the final SEBT score, the length of the lower limb measured from the anterior–superior iliac spine to the medial malleolus at the supine position will be used to divide the reach distance using the method described previously [60]. Besides, changes in SEBT scores will be examined to see if they reach the minimal detectable change in eight directions, including 6.73% (medial), 8.56 (anterior), 8.68 (anteromedial), 9.69 (anterolateral), 12.17 (lateral), 13.00 (posterior), 13.33 (posterolateral) and 13.36% (posteromedial) [61].

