### Statistics analysis

As all outcomes are continuous variables, they will be presented as mean ± standard deviation. The normality of variables will be tested by the Shapiro–Wilk test. All statistical analyses will be carried out using the SPSS software (Version 22.0, IBM Corp., Armonk, NY, USA) and *p* < 0.05 will be considered as a significant difference. Bonferroni adjustment will be performed in post-hoc analysis when statistical significance is found. A 1-way ANOVA analysis will be conducted to compare outcomes among the four groups. Pearson's correlation coefficient will be calculated to evaluate the relationship between alterations in sensorimotor function and plastic changes in the brain. The effect size (Cohen’s d, 95% confidence intervals) will be calculated to evaluate the magnitude of difference among groups. Ranges 0.2–0.49, 0.5–0.79, and > 0.8 are considered as small, medium, and large effect sizes respectively. A 2-way repeated-measure ANOVA analysis will be performed in terms of the different time points (i.e., baseline, post-test, and 2-week follow-up) of the various groups (i.e., WBVBT, BT, WBV, and control group). A correlation analysis will be conducted to determine the relationship between changes in sensorimotor deficits and neural plasticity. To estimate the efficacy and effectiveness of interventions, per‑protocol and intention-to-treat analysis will be conducted respectively if any participants withdraw.

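### The Abstract, the outcome text and Table 2 give different primary outcomes, and even the narrowest version has two endpoints at 0.05 with no rule to hold the overall error at 5%

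*Protocol article*

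**What the plan says.** Three places in the protocol article define the primary outcome.

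- **Abstract, Methods:** "Primary outcome measures are sensorimotor function including strength, balance, proprioception and functional performance". The brain measures (TMS, then fNIRS) follow in separate sentences without the word primary.
- **Outcome measures, text:** "The primary outcome measures will be balance with SEBT end-point to determine sensorimotor deficit, and activation of brain area with oxyhemoglobin". Strength, proprioception and functional performance are no longer primary, and a brain measure is.
- **Outcome measures, Table 2:** the primary block holds TMS, fNIRS, SEBT with the Time-In-Balance Test (TIBT), strength, AMEDA and the side-hop test. Only the CAIT and the FAAM are secondary.

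The components are described later. Sensorimotor deficits says "There will be 8-direction including anterior, anteromedial, medial, posteromedial, posterior, posterolateral, lateral and anterolateral in the SEBT test", and adds that "changes in SEBT scores will be examined to see if they reach the minimal detectable change in eight directions". Brain plasticity has HbO recorded over three cortical regions, in one-legged stance with eyes open and with eyes closed.

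Statistics analysis sets one significance threshold, 0.05, for all analyses. It plans a one-way ANOVA across the four groups and a two-way repeated-measures ANOVA over the three time points. Its only statement on multiple testing is "Bonferroni adjustment will be performed in post-hoc analysis when statistical significance is found". Sample size uses α 0.05 with no division between endpoints.

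**The concern.** The three lists differ in substance. TMS is primary only in Table 2. HbO is primary in the text and the table but not in the Abstract. Strength is primary in the Abstract and the table but not in the text. If SEBT and HbO show nothing, a result on strength, side-hop or TMS could still be reported as primary, with support from the printed protocol.

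The testing rule does not close this gap. A Bonferroni step that starts only once a result is significant cannot control the chance of getting that first result on one of several endpoints. With two primaries each at 0.05 and no statement of what counts as success, a positive result on either can be claimed, and the overall error rate exceeds 5%.

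**Working it through.** **1. The three definitions side by side**

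| Measure | Abstract | Outcome measures text | Table 2 |
|---|---|---|---|
| SEBT | within balance | primary | primary |
| TIBT | within balance | not named | primary |
| Strength | primary | not named | primary |
| Proprioception | primary | not named | primary |
| Functional performance | primary | not named | primary |
| fNIRS HbO | not called primary | primary | primary |
| TMS | not called primary | not named | primary |

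No two columns agree.

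**2. The plan's own sample size.** Sample size gives f = 0.35, α = 0.05, power 0.8, 4 groups and 3 measurements. The correlation between measurements is not given; 0.5 is assumed here. For the between-groups test, λ = f²·N·m / (1 + (m − 1)ρ) = 0.1225 × 64 × 3 / 2 = 11.76, with 3 and 60 degrees of freedom. Power is 80.5% at N = 64 and 77.4% at N = 60, so the stated 64 is reproduced. Then 64 / 0.8 = 80, as stated. This is the size for one test at 0.05.

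**3. Narrowest reading: two endpoints, each at 0.05**

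- Independent: 1 − 0.95² = 9.75%.
- Correlated: simulating four arms of 20 with one F test per endpoint gives about 8% at correlation 0.8.

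**4. If components were tested one by one (conditional).** There are 8 SEBT directions and 3 regions × 2 stance conditions = 6 HbO results, so 14 tests.

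- Independent: 1 − 0.95¹⁴ = 51%.
- Same simulation, common correlation 0.8: about 21%.

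**5. If everything in Table 2 were tested (conditional, for scale only).** Sensorimotor: SEBT 8, TIBT 1, strength 4, AMEDA 1, landing version of that test (AIDAL) 1, side-hop 1, making 16. TMS: 5 measures × 2 muscles = 10. HbO: 6. Total 32.

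- Independent: 1 − 0.95³² = 81%.
- Common correlation 0.8: about 28%.
- AIDAL is in the text but not in Table 2. Without it, 1 − 0.95³¹ = 80%.

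The correlations in steps 3 to 5 are assumptions; the protocol gives none.

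**6. Cost of splitting alpha.** Using the formula in step 2 with α = 0.025, power at N = 64 is 71%. Reaching 80% needs N = 76, or 76 / 0.8 = 95 after dropout.

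**The case against.** The strongest reply is that the multiplicity may be much smaller than the number of components suggests. The text speaks of an SEBT end-point and a final score, both singular, and refers to a published scoring method that is not at hand, so a composite cannot be ruled out. The per-direction minimal detectable changes are introduced as an extra check, not as eight hypothesis tests. How HbO is summarised may properly be left to a fuller plan. All of this stands. A reader might infer that the protocol commits to 14 tests at 0.05, or that its error rate is 21% to 51%, but the document supports neither. Those figures apply only if the components are tested separately.

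A reader might also infer that the two post-baseline visits raise the error further. That does not follow, because the repeated-measures ANOVA takes all three time points together and one group or group-by-time test covers both visits. Visits would add tests only if the one-way ANOVA were run at each, which is not stated.

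The Abstract could be read as agreeing with Table 2, since it names TMS and fNIRS before turning to secondary outcomes. But its primary label covers only sensorimotor function, and on this reading the narrower outcome text still conflicts with both.

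Finally, SEBT and HbO address different questions, so whether they form one error family is partly a matter of judgement. Two co-primaries also need no correction if both must be significant. Neither position is stated, so neither protects the error rate as the protocol stands.

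**Conclusion.** The concern holds. The definitions of the primary outcome contradict one another and nothing in the document reconciles them. An unseen analysis plan may add detail, but it would not make these published statements agree.

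The error inflation that can be asserted is the one for two endpoints: about 8% to 10% instead of 5%, and 9.75% if they are independent. It assumes that success on either endpoint counts, which the protocol leaves open. The larger figures (about 21% to 51% for 14 tests, higher for the Table 2 list) are conditional on component-wise testing and on assumed correlations from 0.8 down to 0. The conclusion does not depend on them.

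**What to change.** - **One definition.** Use the same primary outcome statement in the Abstract, the Outcome measures text and Table 2.
- **One score per endpoint.** Name a single SEBT score, for example the mean of the eight leg-length-normalised reaches, and a single HbO summary with its region and stance condition. Make all other measures and the single directions secondary.
- **One contrast.** Say whether the primary comparison is at one visit or is the repeated-measures group-by-time test.
- **One error rule.** Name one single primary, or require both to be significant, or test the two in a prespecified order, each at 0.05. Which to choose is a design decision for the investigators. Fixed order makes the second endpoint conditional on the first, which matters because the Discussion calls the role of brain plasticity the main purpose.

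This is mainly a change of wording, best made before any outcome data are analysed. The price is that the other outcomes lose confirmatory status.

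Two choices also affect power. If alpha is split at 0.025 each, the sample size section should state about 71% at N = 64, or raise N to 76 (95 after dropout), with f 0.35 and an assumed correlation of 0.5. And since 64 is reproduced by the between-groups test over three measurements, power should be restated if another contrast is chosen. A one-way comparison at a single visit with the same f has about 61% at N = 64.
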